## Abstract

**Background:**

Many older people presenting to Acute Medical Units (AMU) are discharged after only a short stay (< 72 hours), yet many re-present to hospital or die within 1 year. Comprehensive Geriatric Assessment may improve patient outcomes for this group.

**Method:**

**Trial Registration:**

ISRCTN: ISRCTN21800480

## Background

Early and rapid hospital triage of patients with medical crises is undertaken in Acute Medical Units (AMUs) in the UK. Ninety-eight per cent of UK NHS hospitals have AMUs [1]. Many patients in AMUs have a very short length of stay (< 1-2 days) [2]. At least 10% of all attendees will be frail older people, identified by the presence of one or more geriatric syndromes [3,4]. Frail older people who present with a crisis to an AMU but who are discharged rapidly have poor outcomes: 58% subsequently re-present to the AMU and 29% die over the 12 months from the index presentation [4]. Hospital facilities are expensive and a hospital stay is usually the most costly episode in the patient's experience of care. Managers and clinicians are therefore under pressure to reduce avoidable hospital admissions. Despite a multitude of efforts to reduce hospital attendance and admission, the numbers are increasing year on year [5].

There is a considerable body of evidence supporting the effectiveness of complex interventions for frail older people in general [6], particularly Comprehensive Geriatric Assessment (CGA) [6,7]. However, delivering CGA in the context of an AMU is challenging - time, bed pressures and lack of appropriate expertise are all barriers - and a recent review of the literature was unable to identify any trials of CGA being delivered in AMUs [8].

We have clinically piloted a version of CGA suitable for use in older people presenting to AMUs, "interface geriatrics", in which a geriatrician makes a clinical assessment of older patients being discharged from an AMU, and plans any necessary aftercare including further assessment at home and liaison with primary care, intermediate care and specialist community services. This study will evaluate interface geriatrics compared with current management, using a randomised controlled trial with economic analysis.

## Objectives

The objective of the study is to examine if the intervention increases the number of days spent at home in high risk older patients discharged from an acute medical unit, over current management, and whether it is cost effective.

## Method

A multicentre randomised controlled trial will be conducted. After informed consent and baseline data have been collected, participants will be randomised to usual care or the intervention arm, see Figure 1.

**Figure 1 F1:**
[figure not shown]
**Overall study outline of a comprehensive geriatric assessment intervention randomised controlled trial**. This illustrates the processes involved in a randomised controlled trial comparing comprehensive geriatrician assessment and intervention over current management for high risk older patients discharged from an acute medical unit.

### Participants

Patient participants will be patients who have been cared for on the AMU for less than 72 hours at the point of discharge, at either of two recruiting centres. Participants will be aged 70 years or over, and will be at high risk of future health problems as evidenced by a score ≥2/6 on the Identification of Seniors At Risk (ISAR) tool [9]. Patients excluded from the study will be: those not resident in the usual hospital catchment area; those without mental capacity to give informed consent and where there is no consultee available; those in whom an exceptional reason is cited by AMU staff why they should not be recruited (e.g. dangerous); and participants already participating in another intervention research project. Figure 2 shows the recruitment algorithm to be used depending upon the presence or absence of capacity to consent to the study, and the presence or absence of a carer.

**Figure 2 F2:**
[figure not shown]
**Recruitment algorithm of a comprehensive geriatric assessment intervention randomised controlled trial**. This figure illustrates the recruitment algorithm to be used depending upon the presence or absence of capacity to consent to the study, and the presence or absence of a carer.

Carer participants will be those identified as a carer of a patient participant by the patient participant or from the patient participant's clinical records.

### Baseline data

Baseline data for patient participants will comprise:

• Demographics: age, gender, ethnicity, marital status, residential status, education, social & financial questions

• Contacts and follow up information: usual and discharge (if different) address & telephone number, GP contact details

• ISAR score

• Health conditions: presenting problems, comorbidities and list of medications

• Cognitive function: Folstein MMSE [10]

• Personal ADL function: Barthel ADL Index [11]

• Health status: EuroQoL EQ5D [12] and ICECAP [13]

• Psychological well-being: GHQ-12 [14]

• Active receipt of palliative care services

• Resource use: health care (primary, secondary, intermediate and emergency services) and social services

Baseline data for carer participants will comprise:

• Carer strain: Caregiver Strain Index [15]

• Carer specific quality of life: CQLI-R [16]

• Health status: EuroQol EQ5D [12]

### Interventions

Standard care on the AMUs prior to recruitment for both the control and intervention groups will comprise an assessment by a consultant physician and attending medical team. Some patients will be assessed by members of a multidisciplinary team (physiotherapist, occupational therapist, nurse), as deemed appropriate by the AMU team.

Participants in the control group will receive no additional intervention over and above usual care after randomisation. Usual care is usually directed by the patient's general practitioner, but on some occasions will also include follow up and investigation by the acute medical team.

Participants in the intervention group will have an assessment by a geriatrician, who will also deliver or involve other agencies in the delivery of whatever aftercare they deem is necessary which may include: a review of diagnoses; a medication review; further assessment at home or in a clinic; advance care planning; and liaison with primary care, intermediate care and specialist community services. The intervention will commence immediately prior to discharge whilst on the AMU, continuing in the community and is largely expected to be complete within one month of randomisation.

### Clinical outcomes

The primary outcome will be "days at home". This will be calculated as 90 days from randomisation minus the number of days in this period each participant is in residential intermediate care units, in hospital (community hospital, psychiatric hospital or other acute hospital), in respite care or in a new care home placement or deceased [17]. This continuous outcome takes into account many different adverse outcomes including death and hospital re-admission or diversion to other settings as a result of health needs. This outcome will be ascertained from direct follow up of the participant, health and social service databases. Secondary outcomes will comprise:

• Death

• Institutionalisation

• Secondary care contacts (Emergency Department, AMU admissions, clinics)

• Personal Activities of Daily Living (Barthel ADL Index) [11]

• Self-reported falls over previous 90 days

• Psychological well-being (General Health Questionnaire, GHQ-12 [14])

• Health status (EQ5D [12] & ICECAP [18])

• Resource use and associated costs

• Carer strain: Caregiver Strain Index [15]

• Generic quality of life: EuroQol - EQ5D [12]

• Carer specific quality of life: CQLI-R [16]

Outcome measures will be collected by post, by phone or in person if necessary by a trained researcher not involved in the recruitment process and blind to allocation.

### Resource use

Costs will be estimated for each patient participant based upon health and social service resource use. Table 1 lists the resource use items that will be measured, how they will be determined, and what unit cost will be applied to them.

**Table 1 T1:** Summary of resource use data to be collected

Parameters	Source	Unit costs
*Baseline primary care resource use per week*: home visit (community matron, specialist nurse, district nurse), attendance at day care centre, out-of-hours services	Clinical records via GP systems*	NHS and PSSRU reference costs
*Baseline personal social services per week: *home help, cleaner, private carer, community care assistant	Patient/carer participant report	
*Index intervention resource use*: length of stay and key interventions.	In situ data collection (clinical records or equivalent hospital systems)*	
*Follow up secondary care resource use*: clinic appointments and category of appointment; inpatient days and category of admission; A&E visits attendance at day hospital	In situ data collection (clinical records or equivalent hospital systems)*	
*Follow up use of emergency services* Paramedic and non-paramedic attended	Clinical records via ambulance service systems*	
*Follow up primary care resource use*: GP appointments; home visit (community matron, district nurse, specialist nurse), attendance at day care centre out-of-hours services admission to care home^	Clinical records via GP systems*	
*Follow up mental health resource use*: CPN visits Mental health admissions	Clinical records via mental health trust systems*	
*Follow up intermediate care resource use per week*: Home visits Admissions	Clinical records via intermediate care systems*	
*Personal social services:* home help, cleaner, private carer, community care assistant	Social services records and patient/carer participant report	

*Queries will be generated for the different data systems, to extract patient participant-based activity from baseline to the end of the follow-up period.

The cost of the interface geriatrician will be derived from a time log, kept by the participating geriatricians, of time spent on direct patient care activities (face to face contact and any other patient-related activities). Additional information on resource use will be collected on all participants in both arms (Table 1).

### Sample size

The primary outcome is the number of days spent at home in the 90 days after randomisation. Pilot data in a similar population demonstrated the mean number of days spent at home at 90 days was 63 with a standard deviation of 23 days. Using these data, a sample size of 200 in each group will have 90% power to detect a difference in the mean number of days at home of 7.5 days between the two groups (control group mean of 63 days and intervention group mean of 70.5 days) using a two-group t-test with a 5% significance level.

As days at home accounts for loss to follow up from events such as death, we will only need to slightly over-recruit to account for participants who withdraw completely for from the study (< 5% based on recruitment to date). Accordingly we aim to recruit up to 420 individuals overall.

### Randomisation

Participants will be randomly allocated using a 1:1 ratio to either the control group or to the intervention group. Randomisation will be stratified by centre.

### Sequence generation

A computer generated pseudo-random list using random permuted blocks of randomly varying size will be used. Access to the sequence will be confined to the Nottingham Clinical Trials Support Unit (CTSU) Data Manager.

### Implementation

The randomisation sequence will be created by the Nottingham CTSU http://ctu.nottingham.ac.uk/ctu in accordance with their standard operating procedures and held on a secure server. Investigators will access the treatment allocation for each subject by means of a remote, internet-based randomisation system developed and maintained by the Nottingham CTSU. The sequence of treatment allocations will be concealed from the researchers collecting the outcome data and the statistician until statistical analyses are complete.

### Blinding

It is not possible to blind participants to the intervention in this study, but outcomes will be collected by researchers who are blind to allocation and all analyses will be carried out blind to allocation.

### Statistical methods

#### Descriptive statistics

Continuous data that are approximately normally distributed will be summarised in terms of the mean, standard deviation; minimum, maximum and number of observations. Skewed data will be presented in terms of the median, lower and upper quartiles, minimum, maximum and number of observations. Categorical data will be summarised in terms of frequency counts and percentages. There will be no test of statistical differences or confidence intervals for differences between the intervention and control groups on any baseline variable, however analyses will be adjusted for prognostically important variables to improve the precision of the estimates of the intervention effect.

#### Univariate and multivariate analysis

The primary analysis will be based on the intention to treat principle, and will compare the primary outcome (days at home) between the two groups either using a two-sided t-test or a Mann-Whitney U test if the assumptions for the t-test are not satisfied, stratified by centre. We will use data from our recently completed cohort study (Acute Medicine Outcome Study) to explore the distribution of days at home in this population, constrained to take values between 0 and 90 days, to determine the most appropriate statistical model for the adjusted analysis. We will also use data from the cohort study to identify prognostically important variables for days at home in advance of the analysis of the randomised controlled trial. The intervention effect parameter will be presented as an estimate with 95% confidence interval.

We will also carry out a per-protocol efficacy analysis, looking at those patients who actually received the intervention.

All continuous secondary outcomes will be analysed using linear regression models, while logistic regression and Poisson regression models will be used for dichotomous and count data, respectively. Mortality will be analysed using Cox proportional hazards regression. All adjusted analyses will include centre in the model and other baseline variables used in these models will be specified in advance of the analysis based on the results of our prior cohort study. All statistical tests will be two-sided and performed using a 5% significance level with no adjustment for multiplicity.

We anticipate a greater recognition of the need for palliative care services in this population and will test for interaction between the intervention and terminal care status. If interaction is present, the results will presented as sub-group analyses. Other pre-specified sub-group analyses will be carried out according to the ISAR score, residency at baseline (care home vs. no care home) and cognition (MMSE ≤27), as these are prognostically important baseline indicators of adverse outcomes.

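### The supplementary per-protocol analysis selects on receipt, an event possible only in the intervention arm, so a comparison with controls can be biased in a direction that depends on how receipt is defined

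*Protocol article*

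**What the plan says.** Under 'Univariate and multivariate analysis' the protocol article sets the main comparison: "The primary analysis will be based on the intention to treat principle, and will compare the primary outcome (days at home) between the two groups". It then adds a second one: "We will also carry out a per-protocol efficacy analysis, looking at those patients who actually received the intervention".

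Three other sections bear on that sentence.

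- **Interventions.** For controls: "Participants in the control group will receive no additional intervention over and above usual care after randomisation". In the intervention arm the geriatrician's work starts on the AMU just before the patient leaves, "continuing in the community and is largely expected to be complete within one month of randomisation". How much is given is a matter of judgement: the assessment is by a geriatrician "who will also deliver or involve other agencies in the delivery of whatever aftercare they deem is necessary".
- **Clinical outcomes.** The primary outcome is defined as follows: "This will be calculated as 90 days from randomisation minus the number of days in this period each participant is in residential intermediate care units". Days in hospital, respite or a new care home, and days after death, are also subtracted.
- **Blinding.** The section says that "all analyses will be carried out blind to allocation". The section headed 'Implementation' likewise conceals the allocations from the statistician until the analyses are finished.

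**The concern.** Receipt happens after randomisation and can happen in one arm only. A set chosen by receipt therefore drops some intervention patients, while the controls who would have been non-receivers cannot be identified and stay in. Whatever separates receivers from non-receivers then enters the estimated effect.

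That selection can be tied to the outcome. The intervention month lies inside the 90-day window, and a patient who dies or is readmitted in that month loses days at home and may also miss the community part. Aftercare is matched to perceived need, so the amount received may itself track prognosis.

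At stake is a result labelled as efficacy, tested at an unadjusted 5%, that could differ from the ITT result through selection alone. Separately, a set chosen by receipt shows which arm is which, and that cannot be squared with every analysis being blind.

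**Working it through.** **Inputs from the article ('Sample size').** Mean 63 days, SD 23, target difference 7.5 days, 200 per group, 90% power, two-sided 5%.

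**The plan's own figure.** The standard error of the difference at 200 per group is 23 × √(2/200) = 2.30 days. Power is Φ(7.5/2.30 − 1.96) = 90.3% by the normal approximation (90.2% by the t-test). The required size is 198 per group (199 by the t-test). The stated 200 reproduces.

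**Inputs that are assumptions.** The article gives neither the share q of the intervention arm that does not receive the intervention nor the mean m of their days at home. Both are varied below.

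**Bias with no true effect.** Both arms average 63 days, all controls are kept, and non-receivers are dropped from the intervention arm:

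- receiver mean = (63 − q·m)/(1 − q)
- bias = receiver mean − 63
- standard error ≈ 23 × √(1/200 + 1/[200(1 − q)])
- the false-positive rate follows from bias/standard error against ±1.96

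| q | m | Receiver mean | Bias (days) | Share of 7.5 | False-positive rate |
|---|---|---|---|---|---|
| 5% | 45 | 63.9 | +0.9 | 13% | 7% |
| 10% | 50 | 64.4 | +1.4 | 19% | 9% |
| 15% | 45 | 66.2 | +3.2 | 42% | 26% |
| 20% | 40 | 68.8 | +5.8 | 77% | 65% |
| any | 63 | 63.0 | 0 | 0% | 5% |
| 5% | 80 | 62.1 | −0.9 | −12% | 7% |
| 10% | 80 | 61.1 | −1.9 | −25% | 13% |
| 15% | 80 | 60.0 | −3.0 | −40% | 24% |

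Two rows in full: (63 − 0.20 × 40)/0.80 = 55/0.80 = 68.75, a bias of +5.75; and (63 − 0.15 × 80)/0.85 = 51/0.85 = 60.0, a bias of −3.0. The positive rows are not a bound: at q = 5% and m = 50 the bias is 60.5/0.95 − 63 = +0.7.

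**What decides the sign.**

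- Receipt means the community phase or completion: early deaths and readmissions tend to be excluded, m falls below 63 and the bias is positive.
- Receipt means any geriatrician contact before discharge: patients who fail after discharge have already received it, q is small and so is the bias.
- Non-receipt reflects little perceived need: m exceeds 63 and the bias is negative.

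**The alternative estimator.** Complier average causal effect = ITT difference in means ÷ (share receiving in the intervention arm − share receiving in the control arm). With no true effect the numerator is zero on average whatever q and m are, so the selection bias in the table does not arise. With no receipt among controls, its standard error is about 2.30/(1 − q): 2.42 at q = 5%, 2.56 at 10%, 2.88 at 20%.

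**The case against.** The strongest reply is that the mechanism depends on a definition the article does not give. Contact begins before discharge. If that contact counts as receipt, patients who die or are readmitted later remain in the set, and little is lost. **This stands.** A reader might infer that the analysis removes early failures and so always favours the intervention. The documents do not support that, and non-receivers with less need would reverse the sign.

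It can also be said that the comparator is not stated, and that the definition, comparator and estimator of a supplementary analysis are commonly left to a statistical analysis plan, which is not shown. This stands in part. The missing definition is not a fault, and the comparison with all controls is an inference, so the point is put conditionally. The stated rule remains: it selects on receipt, and only intervention patients can fail it. A later definition would change the size of the bias, not that asymmetry.

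Third, the analysis is secondary to ITT, and nothing in the article gives it a role in the trial's conclusion. This stands and limits the weight of the point. A reader might infer that the main result is compromised; it is not.

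Finally, the article does not say whether controls might see a geriatrician in usual care or after readmission, so one-sided non-receipt cannot be taken for granted. This stands, and the fix includes a check.

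**Conclusion.** The point holds in conditional form. The rule as worded selects on a post-randomisation event confined to one arm, so a comparison of receivers with controls is not protected by randomisation and can be biased.

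Under no true effect, the cases worked give about +0.9 to +5.8 days when the excluded 5-20% average 40-50 days (with 5% at 45 days as the low case), zero when they average 63, and −0.9 to −3.0 days when 5-15% are excluded averaging 80. These sizes rest on assumed shares and means and on keeping all controls. They show what the rule could do and do not estimate what it will do in this trial.

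The conflict with the blinding statements does not depend on the direction of bias: a dataset chosen by receipt identifies the intervention arm. Because ITT is primary and unaffected, this is an inexpensive improvement to a supplementary analysis, not a threat to the trial's main conclusion.

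**What to change.** 1. Define receipt as the initial geriatrician assessment. The geriatricians' time logs, already planned for costing under 'Resource use', can supply it.
2. In place of the receipt-selected comparison, estimate a complier average causal effect on mean days at home, with randomised arm as the instrument, adjusted for centre and the baseline covariates pre-specified for the adjusted analysis. If the receipt-selected comparison is kept, label it clearly as exploratory.
3. State the exclusion restriction: allocation affects days at home only through receipt. It is easier to defend when receipt is the initial assessment than when it is completion, since patients treated in part may still benefit.
4. Check and report whether any controls received the intervention. If some did, use the difference in receipt between arms as the denominator and state the added assumption that allocation made nobody less likely to receive it.
5. Run this after the blinded ITT analysis is locked, and limit the statements under 'Implementation' and 'Blinding' to the ITT analyses.

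The cost is a few lines of code, the stated assumption, and an interval wider than that of the ITT difference by a factor of about 1/(1 − q): 5% wider at q = 5% and 25% wider at q = 20%.

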#### Economic analyses

Costs will be constructed from the perspective of the NHS and personal social services (PSS). 90 days of resource data will be collected for each patient participant. Costs will be estimated for each patient participant in the study. The costs will be calculated as resource use multiplied by the unit cost of the specific resource.

Health and social care resource use data will be valued using published unit cost data [19].

A cost-effectiveness analysis comparing specialist geriatric assessment, intervention and community-based follow-up following on from an acute admission to standard care will be carried out. Benefits to the patient participant will be measured with Quality-Adjusted Life Years (QALYs), which will be generated using EQ5D data, assuming homogeneity across treatment groups in any insensitivity of the EQ5D to our patient participants. The time horizon of the economic analysis will incorporate the lifetime of the cohort, through extrapolation of quality-adjusted survival from the end of the intervention period. These will be combined with cost data to generate incremental cost effectiveness ratios and Incremental Net Benefit (INB) statistics [20].

No discounting of intervention costs will be necessary as the intervention period is less than 12 months. QALYs will be discounted at 3.5%. Incremental cost-effectiveness analysis will be undertaken in the absence of convincing dominance by any treatment alternative. Probabilistic sensitivity analyses and cost-effectiveness acceptability curves will used to assess the risks posed by uncertainty in the estimated incremental net benefit statistics. Value of information and value of distributional information analyses will also be undertaken if appropriate.

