#### Procedures for missing, unused and spurious data

If there is less than 5% missing data we will use the complete dataset but where there is more than 5% missing data our preferred method will be multiple imputation. We will use the multiple imputation procedures in Stata to impute missing values, including all baseline variables. We will then combine the results using Rubin's rules [21] for multiply imputed data.

Additionally we will assess the baseline characteristics of those who have dropped out or with large amounts of missing data in order to see if there is any differential loss to follow up which may result in bias.

Where extreme outliers are identified during model checking, sensitivity analyses will be carried out including and excluding the extreme outliers in order to test the robustness of the findings.

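### Poisson regression is fixed for count secondary outcomes with no provision for overdispersion, so intervals for repeat hospital contacts are likely to be too narrow

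*Protocol article*

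**What the plan says.** The protocol article (Statistical methods, Univariate and multivariate analysis) assigns a model to each type of secondary outcome. Continuous outcomes get linear regression, and for the rest "logistic regression and Poisson regression models will be used for dichotomous and count data, respectively". Death is handled separately: "Mortality will be analysed using Cox proportional hazards regression". Adjusted models are to contain centre and baseline variables chosen beforehand from the earlier cohort study. On testing: "All statistical tests will be two-sided and performed using a 5% significance level with no adjustment for multiplicity".

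Two items in the list under Clinical outcomes could yield counts: "Secondary care contacts (Emergency Department, AMU admissions, clinics") and "Self-reported falls over previous 90 days". Neither is defined there as a count or as yes/no.

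The only model checking mentioned is under Procedures for missing, unused and spurious data: "Where extreme outliers are identified during model checking, sensitivity analyses will be carried out". Dispersion is not named. No section gives a mean, variance or dispersion for any count outcome.

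**The concern.** A Poisson model takes the variance to equal the mean, and its model-based standard errors rely on that. When people differ in their underlying event rate, or when one crisis produces several contacts in a chain, the variance exceeds the mean and those standard errors are too small.

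The article describes such a population. Emergency department visits, AMU admissions and clinic visits are grouped under one outcome and can follow one another. ISAR score, care-home residence and cognition are named as prognostic, so risk is mixed. Planned covariates remove only the measured part of that variation.

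The primary outcome has a fallback if the t-test assumptions fail, and cohort data will be used to study its distribution. The count outcomes have neither. With no multiplicity adjustment, nothing elsewhere in the plan absorbs an inflated error rate. Reducing avoidable hospital use is part of the trial's stated motivation, so readers will look at the contact results.

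**Working it through.** **The plan's own figure.** The article gives no figure for count outcomes. Its one design figure is 200 per group for days at home (difference 7.5, SD 23, 90% power, two-sided 5%). The normal formula gives 2 × (1.960 + 1.282)² × 23² / 7.5² ≈ 198 per group, and power at 200 is 90.3%, so the figure reproduces. It is used below only to set the simulated trial size.

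**Inputs.**
- Model, level and absence of multiplicity adjustment: Univariate and multivariate analysis.
- 90-day period: Clinical outcomes and Economic analyses ("90 days of resource data will be collected for each patient participant").
- Mortality: Background ("58% subsequently re-present to the AMU and 29% die over the 12 months from the index presentation").
- Residual variance/mean ratio φ: **assumed**, 1.25 to 4.

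**Step 1: why mixed risk raises φ.** If each person has rate λ with mean μ, the count has variance μ + Var(λ), so φ = 1 + Var(λ)/μ. Any variation in λ that the covariates do not explain gives φ above 1.

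**Step 2: effect on intervals and tests.** The Poisson standard error is too small by a factor 1/√φ. A nominal 5% test therefore has true size 2 × [1 − Φ(1.96/√φ)].

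**Step 3: check by simulation.** 200 per arm, gamma-Poisson counts, no true effect, 10% mortality in both arms, 5,000 runs per setting (Monte Carlo error about 0.3 percentage points). The simulated columns have no offset for time alive.

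| φ (assumed) | 1.96/√φ | Interval width relative to correct | Type I error, formula | Type I error, simulated plain Poisson | Type I error, simulated robust SE |
|---|---|---|---|---|---|
| 1 | 1.960 | 1.00 | 5.0% | 5.1% | 5.0% |
| 1.25 | 1.753 | 0.89 | 8.0% | 8.2% | 5.4% |
| 1.5 | 1.600 | 0.82 | 11.0% | 10.8% | 5.1% |
| 2 | 1.386 | 0.71 | 16.6% | 16.4% | 5.2% |
| 3 | 1.132 | 0.58 | 25.8% | 26.0% | 5.6% |
| 4 | 0.980 | 0.50 | 32.7% | 31.8% | 5.3% |

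The simulated ratios were close to the row values (1.01, 1.26, 1.50, 2.01, 3.00, 3.98). Formula and simulation agree, and robust standard errors bring the error back close to 5%.

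**Step 4: does time alive affect interval width?** At φ = 2 with equal mortality, plain Poisson has type I error 16.4% without an offset and 15.8% with one. With no overdispersion and equal mortality, leaving the offset out gives 5.1% to 5.2%. So an offset neither causes nor cures the problem in Step 2.

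**Step 5: size of the time-alive issue.** Under an assumed constant hazard, 29% mortality at 12 months gives 1 − 0.71^(90/365) = 8.1% by day 90. With deaths spread evenly over the period, about 8.1%/2 ≈ 4% of person-time is lost. If the arms lose equal amounts, the rate ratio is unchanged. If mortality differs (assumed splits), a true ratio of 1 per day alive becomes, per person:
- 10% vs 5%: 0.975/0.950 = 1.026 (simulated 1.024)
- 15% vs 10%: 0.950/0.925 = 1.027 (simulated 1.027)
- 15% vs 5%: 0.975/0.925 = 1.054 (simulated 1.056)

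Judged against that per-day-alive null, plain Poisson without overdispersion rejects in 5.5%, 5.9% and 8.8% of runs.

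**The case against.** The strongest reply is that this is a journal article. One sentence names a model family for each outcome type, and the variance estimator is commonly left to the full protocol or SAP, which are not shown. Naming Poisson does not exclude robust standard errors. This stands in part: the article does not address overdispersion, but a reader who infers a decision to ignore it goes beyond the text. It does not dispose of the point, because the model is a stated choice and, applied as written, has a doubtful variance assumption for these data. The outlier sensitivity analysis does not correct Poisson standard errors.

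Second, the dispersion is assumed, and the planned adjustment will lower it by an unknown amount. This stands. The inflation is conditional, which is why the range starts at 1.25.

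Third, falls are not stated to be a count. This stands too. A yes/no version would go to logistic regression. Because falls are self-reported in retrospect, death there is mainly a missing-outcome problem. Contacts carry the point, although they are not expressly defined as counts either.

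A reader might also infer that leaving out time alive makes intervals too narrow, or seriously biases the comparison. The checks do not support that. Width is unaffected, and the shift is about 2% to 6%, arising only if mortality differs between arms. Contacts per randomised person over a fixed 90 days is a legitimate estimand, and death already enters the primary outcome and has its own Cox model.

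**Conclusion.** The point holds for count secondary outcomes, most clearly secondary care contacts. The article fixes Poisson regression and states no safeguard against a variance above the mean, which is likely here. Without a safeguard, a nominal 5% test would have a true error of about 8% at a variance/mean ratio of 1.25, 17% at 2 and 33% at 4.

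This rests on three conditions: the outcomes are analysed as counts, the residual dispersion lies in the assumed range, and model-based standard errors are used. The article settles none of these, so the size is a range and not a prediction for this trial. The handling of time alive is a minor question of estimand and is not part of the fault. The primary comparison of days at home and its sample size are untouched.

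**What to change.** State in the analysis plan that count outcomes will be analysed by Poisson regression with robust (sandwich) standard errors, or by negative binomial regression, with the centre and baseline adjustment already planned, and report rate ratios with 95% confidence intervals. The simulation above tested the robust Poisson version. Say also which outcomes are counts, in particular whether falls are a number or yes/no. The choice should be made before the trial data are analysed; the cohort study could be used to look at dispersion if it recorded these counts.

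State whether the target is contacts per person over 90 days or per day alive. If it is the former, a model with log(days alive) as offset can serve as a sensitivity analysis.

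The cost is a few sentences and no new data, since the primary outcome and the Cox model already need dates of death. Intervals become wider by about √φ: 1.12 times at a ratio of 1.25, 1.41 times at 2 and 2 times at 4. That width reflects the real uncertainty, and some nominally significant secondary results may be lost. The sample size does not change.
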